#### *1. Event based approach*

The onset of an exacerbation will be the first day of an unscheduled health care contact with a GP/pulmonologist due to a COPD exacerbation and the start of additional medication intake or the first day of an unscheduled hospitalisation or emergency visit to the hospital due to an exacerbation. The exacerbation lasts until the last day of this extra medication intake or until the last day of hospital admission [45]. To identify these events, physical therapists will monitor patients’ reasons for absenteeism on physical therapy appointments and relapse in treatment (as an exacerbation might be the reason). In addition, records of health care contacts and additional medication use due to COPD are registered on patients’ prospective daily diary cards. Overall, good compliance to register for instance symptoms, can be achieved using daily diaries in COPD [47].

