In this RCT full blinding of the patients and physical therapists is not feasible. However, Hawthorne effects are non-differential, since patients in the experimental group as well as patients in the control group will get attention from their physical therapist. Both groups receive periodic questionnaires and measurement sessions, avoiding non-random effect optimisation. Several measures are taken to avoid bias due to blinding issues. Although patients will be aware of the existence of two treatment arms, they are not informed about the exact content of the other treatment arm (e.g. determining intensity) to prevent influence on outcomes. The control group will be assessed at the same time intervals as the experimental group by trained physical therapists that do not assess the patients in the experimental group at the same time. The researcher is fully blinded, because all outcome measures are quantified by the patients and physical therapists. Physical therapists are blinded for a number of outcomes measurements (questionnaires CCQ, CRQ-SR, GPE, EQ-5D, DS14 and physical activity level), since part of the data that are provided by the patient alone and will be captured through an electronic patient record system. Moreover, a number of important objective outcomes (exacerbation frequency, duration and severity, mechanically assessed physical activity level and cost diaries) are less liable to patient manipulation in order to please their physical therapist, as these outcomes are directly collected by the researcher.

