	** *Intervention* **	** *Content* **	** *Intensity* **	** *Frequency* **	** *Start* **
Cohort	**Guideline-directed physical therapy (gdPT):**	One or more of:	Ranging on the full intensity scale	On average:	
		Exercise training, peripheral muscle strength training, respiratory muscle training, breathing exercises, electrical muscle stimulation, physical activity in daily life (homework)		30 minutes to 1 hour	
	A programme made by individual PTs, within the limitations of the KNFG physical therapy guideline for COPD (usual care)				
				1 to 3 times a week	
				During 3 months to multiple years	
RCT experimental group	**Protocol-directed physical therapy (pdPT):**	Both exercise training and peripheral muscle strength training;	Endurance/ interval training ≥ 60% of (sub) maximum, muscle strength training ≥ 80% of maximum, always: borg-scale ≥5	Minimal:	*Early* PT: starting within 56 days after an acute exacerbation
				1 hour	
	A complete programme by protocol, according to the KNGF physical therapy guideline for COPD, but with strict conditions			Twice a week	
		When indicated: respiratory muscle training, breathing exercises, electrical muscle stimulation		During 12 months	
		Always: physical activity in daily life (homework)			
RCT control group	**Sham-treatment (ST):**	One-time consultation: advice to be physically active in daily life			
	No physical therapy				
	*Or*				
				Maximal:	
	Very low-intensity exercise training	Exercise training only	Endurance/ interval training ≤ 15% of (sub) maximum or borg-scale ≤2	30 minutes	
				Once a week	
				During 12 months	

Definition of abbreviations: RCT = randomised controlled trail; COPD = chronic obstructive pulmonary disease; KNGF = the Dutch Society for Physical Therapy.

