#### *Experimental group*

Patients in the experimental group receive protocol-directed physical therapy (pdPT). The content of the pdPT is based on the on the KNGF physical therapy guidelines for COPD, like the guideline-directed physical therapy in the cohort [35]. However, in the RCT the physical therapy follows a strict protocol. The therapy specifically concerns *early* physical therapy, starting within 56 days after an acute COPD exacerbation. Patients in the experimental group receive a programme of one hour, twice a week for one year. The programme includes high-intensity exercise training, which entails endurance and/or interval training with an intensity of 60% or higher of (sub) maximum physical exertion, based on the results of a maximal cardiopulmonary exercise test (CPET) and six-minute walk test. In addition, ratings of perceived exertion and dyspnoea of five or higher on the modified Borg-scale (0–10) are used to tailor exercise intensity [42]. Peripheral muscle strength training is provided (a programme combining upper and lower extremities) with an intensity of 80% or higher of maximum physical exertion, based on the results of one-repetition maximum tests or handheld dynamometer measurements. Again, ratings of perceived exertion and dyspnoea of five or higher on the modified Borg-scale are used to adjust exercise intensity [9]. When indicated, the programme includes respiratory muscle training, breathing exercises and electrical muscle stimulation. In addition, much emphasis is given to the assessment and treatment of physical inactivity in daily life. Patients are asked to increase their total physical activity on their own. At least 30 minutes of moderately intense physical activity on at least five days a week is the current recommended level. All visits for treatment and all advice for home training are part of standard procedure, following the KNGF guideline physical therapy for COPD and the Dutch Standard for Healthy Exercise (NNGB) [35,43]. An additional file shows the intervention in more detail according to a framework based on the International Classification of Functioning, Disability and Health (ICF) [see Additional file 1] [44].

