#### *Control group*

Patients in the control group receive sham-treatment (ST), which entails no or very low-intensity exercise training, for one year. The latter applies only if the participant in the control group insists on training in a physical therapy practice. The very low-intensity exercise training is limited to a maximum of 30 minutes once a week, with an intensity of 15% or lower of (sub) maximum physical exertion, based on the results of a maximal CPET and six-minute walk test. In addition, ratings of perceived exertion and dyspnoea of two or lower on the modified Borg-scale (0–10) are used to tailor exercise intensity [42]. There will be no further peripheral muscle strength training, respiratory muscle training, breathing exercises nor electrical muscle stimulation [35]. Furthermore, patients will be advised to do at least 30 minutes moderately intense physical activity on their own for at least five days a week according to the physical activity norm [43].

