#### *2. Symptom based approach*

Respiratory symptoms will be monitored using prospective daily diary cards. In these diary cards patients have to report, according to Anthonisen et al. (1987), whether their major symptoms (breathlessness, sputum production, sputum colour) and minor symptoms (cough, wheeze, running nose, score throat, and fever (>38.5°C) were beyond normal [7]. Prospective diary card assessments are best recorded as changes from an agreed baseline, rather than absolute symptom severities. Comparable to the COPE-II study by Effing et al. (2009), at inclusion all patients will receive a ‘what is normal for me’ card, which describes their individual levels of major symptoms at baseline [48]. When patients experience no deterioration of any of the symptoms listed on the diary, they should check ‘no change in symptoms’. When patients experience deterioration, they should check ‘yes’ and report on all symptoms in the diary whether the level of each symptom was ‘normal’, ‘slightly increased’, or ‘clearly increased’.

The onset of an exacerbation will be defined as the first day of at least two consecutive days at which the patient checks ‘clear increase’ from baseline in two major symptoms or one major and one minor symptom. The day that an exacerbation is resolved will be defined as the first day of: (1) three successive days that the patient has returned to his normal health state; or (2) seven consecutive days on which patients continuously reported no or only a ‘slight increase’ in symptoms, compared to baseline, with no fever or change in sputum colour [7,48,49]. Besides the daily diary card, symptoms during COPD exacerbations will also be recorded by the physical therapists, in order to receive additional information about the number and type of perceived symptoms and to add missing information to the daily diary cards in cooperation with the patient.

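### During the treatment year one route for detecting exacerbations runs through therapy contacts, which differ by arm, so the primary rate ratio carries a bias of unknown size and sign

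*Protocol article*

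**What the plan says.** Two routes to the primary count pass through the therapist. Under the event-based approach, "physical therapists will monitor patients’ reasons for absenteeism on physical therapy appointments and relapse in treatment (as an exacerbation might be the reason"; diary records of health-care contacts and extra medication are named as a further source. Under the symptom-based approach, therapists record symptoms during exacerbations and are asked "to add missing information to the daily diary cards in cooperation with the patient". The Data analysis section uses the event-based count, the symptom-based count and a combination of both.

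Scheduled therapy contact differs by arm. On the experimental side: "Patients in the experimental group receive a programme of one hour, twice a week for one year", which Table 1 labels a minimum. For controls, Table 1 gives as the first option "One-time consultation: advice to be physically active in daily life". Low-intensity training is the second option: "The latter applies only if the participant in the control group insists on training in a physical therapy practice", and "The very low-intensity exercise training is limited to a maximum of 30 minutes once a week".

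The Randomisation and blinding section says of exacerbation frequency, duration and severity that "these outcomes are directly collected by the researcher". It also says that "Hawthorne effects are non-differential, since patients in the experimental group as well as patients in the control group will get attention". The same section accepts that patients and therapists cannot be fully blinded.

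**The concern.** A control patient with no appointments cannot miss one, cannot relapse in treatment, and has few occasions on which a therapist could help to repair a diary. A pdPT patient has such an occasion about twice a week. An exacerbation that the patient did not write down is thus more likely to reach the database in one arm than in the other.

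The protocol itself expects incomplete reporting: it notes that event-based recording misses many exacerbations, and it foresees problems with full registration. There is therefore something for extra contact to find.

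Back-filling also matters at the margin. A symptom-based onset needs at least two consecutive days of clear increase, so a single completed or missing day can make or erase an exacerbation. The therapist who helps to supply that day knows the arm.

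The primary rate ratio is at stake. Fuller capture under pdPT would push it towards 1 or beyond; unblinded completion of diaries could push it the other way.

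**Working it through.** **Contacts in the 12-month treatment period**

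- pdPT therapy (Experimental group; Table 1): 2 × 52 = 104 scheduled sessions, before holidays and missed sessions.
- Control therapy (Control group; Table 1): 1 consultation by default, or at most 1 × 52 = 52 sessions. The share of controls who insist on sessions is not given.
- Measurement visits in both arms (Planning of outcome assessment): 3 and 6 weeks, 3, 6 and 12 months = 5.
- Total: 109 against 6 (about 18:1) by default, or 109 against 57 (about 1.9:1) at the control maximum. The scheduled contacts are unequal in every permitted scenario.

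**Sources common to both arms.** The text gives daily diaries, returned monthly, and three-monthly health-care-use questionnaires, both for 24 months. Only the therapist route differs.

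**The plan's effect size.** Size of the study population gives a 22% difference in exacerbation rate without saying whether it is relative or absolute, and gives no control rate. Its 79 per group therefore cannot be uniquely reproduced; 79/0.8 = 98.75 agrees with the 100 planned after drop-out. Below, 22% is read as relative, so the true ratio is taken as 1 − 0.22 = 0.78. This is an assumption.

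**Illustration 1: assumed capture shares.** Observed ratio = 0.78 × (capture in pdPT ÷ capture in control), with control capture 70% throughout. The 24-month column assumes 70% capture in both arms in year 2, because treatment has ended, and constant rates. The pdPT capture is then the mean of the two years.

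| pdPT capture, year 1 | Ratio at 12 months | pdPT mean capture, 2 years | Ratio at 24 months |
|---|---|---|---|
| 75% | 0.78 × 75/70 = 0.84 | 72.5% | 0.78 × 72.5/70 = 0.81 |
| 80% | 0.78 × 80/70 = 0.89 | 75% | 0.78 × 75/70 = 0.84 |
| 90% | 0.78 × 90/70 = 1.00 | 80% | 0.78 × 80/70 = 0.89 |

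**Illustration 2: a milder case, in terms of power.** Assume that the common sources capture 90% in both arms and that therapists recover half of the missed events in pdPT only. Assume Poisson counts, with the control rate set so that 79 per group over 2 years gives 80% power: 7.849 × (1 + 1/0.78) ÷ (79 × 2 × ln(0.78)²) = 1.84 per year.

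- Year 1 only: mean pdPT capture is (95 + 90)/2 = 92.5%, and the observed ratio is 0.78 × 92.5/90 = 0.80. Expected captured counts per patient are 1.836 × 2 × 0.90 = 3.31 (control) and 1.836 × 2 × 0.78 × 0.925 = 2.65 (pdPT). SE = √[(1/3.31 + 1/2.65)/79] = 0.093; z = 0.221/0.093 = 2.38; power is about 66%. With no true effect, the two-sided error is about 6%.
- All 24 months (an upper bound): the observed ratio is 0.78 × 95/90 = 0.82, power is about 56% and the error about 10%.

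**Statements set side by side.** The blinding section attributes collection of exacerbation outcomes to the researcher. The two approach sections give therapists a part in identifying events and completing diaries. The blinding section also explains the researcher's own blinding by saying that patients and therapists quantify all outcomes. These statements cannot all stand as written.

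**The case against.** The strongest reply is that the therapist route is marginal. Patients in both arms keep daily diaries, which record symptoms, health-care contacts and extra medication, and both arms receive the three-monthly questionnaires. Therapists do not fill in the diaries; they only help to add what is missing. They can therefore contribute only what the common sources missed. An event-based exacerbation also requires a physician contact with medication, or a hospital or emergency visit, so a therapist can report one but cannot create one. Study treatment stops after 12 months, while the primary outcome is defined over two years. The Discussion promises standardised monitoring of all groups.

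Most of this stands, and it limits the size of the problem. It does not remove it: no stated procedure equalises the therapist route or takes it out of the count, and the promise of standardised monitoring sits beside a route that is not the same in the two arms.

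Three stronger readings are tempting and not supported.

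- A reader might infer that the rate ratio is uninterpretable. The shared sources speak against that.
- A reader might infer that twenty extra points of capture cancel the planned effect. Under the assumptions above that holds at 12 months only; over two years the ratio would be about 0.89. Moving from 70% to 90% would also require therapists to recover two thirds of everything otherwise missed.
- A reader might infer that the Hawthorne sentence is itself contradicted. It concerns the effect of attention on patients and makes no claim about event detection. It simply cannot be used as evidence that detection is equal.

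**Conclusion.** The point holds in a limited form. If the plan is followed as written, part of the ascertainment of the primary outcome depends on the arm during the treatment year: about 104 scheduled therapy contacts against 1, or at most 52, with five measurement visits added to each. The people operating that route are unblinded.

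The documents give neither the size nor the sign of the resulting bias. All the ratios and power figures shown rest on assumed capture shares, on reading 22% as relative, and, for 24 months, on constant rates and equal capture in year 2. The power figures also assume Poisson counts. They show only that a moderate difference in capture would matter for an effect of the planned size. Both the 12-month and the 24-month analysis are exposed, the first more than the second.

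Separately, the statement that the researcher collects exacerbation outcomes directly conflicts with the two approach sections and must be reconciled with them.

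**What to change.** - Build the primary count from the sources scheduled in both arms: patient-completed diaries returned monthly, and the three-monthly health-care-use questionnaires. The questionnaires cover contacts and medication, so they support the event-based count; the symptom-based count rests on the diaries. Have events classified by someone blind to arm.
- Flag the source of every event and every therapist-added diary entry at the time of data entry, because the source may not be recoverable later. Keep events and entries known only through therapists out of the primary count, and add them in a sensitivity analysis.
- If missing diary days are queried, use the same procedure in both arms.
- Correct the sentence on direct collection by the researcher, and do not cite equal attention as evidence of equal event detection.

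The cost is revised wording, one source flag, some additional missing diary days, and modest query work. No new instrument is needed. The fix is not complete: frequent contact may still prompt better diary keeping under pdPT. The report should acknowledge this residual difference and show diary completeness by arm.

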#### *2. Symptom based approach*

Respiratory symptoms will be monitored using prospective daily diary cards. In these diary cards patients have to report, according to Anthonisen et al. (1987), whether their major symptoms (breathlessness, sputum production, sputum colour) and minor symptoms (cough, wheeze, running nose, score throat, and fever (>38.5°C) were beyond normal [7]. Prospective diary card assessments are best recorded as changes from an agreed baseline, rather than absolute symptom severities. Comparable to the COPE-II study by Effing et al. (2009), at inclusion all patients will receive a ‘what is normal for me’ card, which describes their individual levels of major symptoms at baseline [48]. When patients experience no deterioration of any of the symptoms listed on the diary, they should check ‘no change in symptoms’. When patients experience deterioration, they should check ‘yes’ and report on all symptoms in the diary whether the level of each symptom was ‘normal’, ‘slightly increased’, or ‘clearly increased’.

The onset of an exacerbation will be defined as the first day of at least two consecutive days at which the patient checks ‘clear increase’ from baseline in two major symptoms or one major and one minor symptom. The day that an exacerbation is resolved will be defined as the first day of: (1) three successive days that the patient has returned to his normal health state; or (2) seven consecutive days on which patients continuously reported no or only a ‘slight increase’ in symptoms, compared to baseline, with no fever or change in sputum colour [7,48,49]. Besides the daily diary card, symptoms during COPD exacerbations will also be recorded by the physical therapists, in order to receive additional information about the number and type of perceived symptoms and to add missing information to the daily diary cards in cooperation with the patient.

#### *Secondary outcome measures*

Exacerbation duration is defined as the duration of the medical intervention per occurrence and the number of days with clear increase of respiratory symptoms. For the event based approach: the duration of an exacerbation will be equal to the time of the medical intervention [45]. For the symptom based approach: the duration of an exacerbation will be equal to the time between onset and resolution of exacerbation based on the above mentioned definitions [7,48,49].

Furthermore, a distinction is made between various levels of exacerbation severity. For the event based approach, a scale for exacerbation severity is proposed, which distinguishes two levels of exacerbation severity: (1) mild/moderate and (2) severe. Level one exacerbations can be treated at home by means of a health care contact with a GP/pulmonologist and the start of additional (temporarily) medication intake (e.g. corticosteroids or antibiotics). Level two exacerbations require hospitalisation or an emergency visit to the hospital [45,46]. For the symptom based approach: the severity of an exacerbation day will be calculated with help of symptom scores. The major symptoms are scored as: normal = 0; small increase = 1; or clear increase = 2. The minor symptoms are scored 0, 0.5 and 1, respectively. Sputum colour will be scored as: normal = 0, different from normal = 2; and fever: no = 0, yes = 1. Adding all scores, results in a daily symptom score ranging from 0–11 points. When patients are admitted to the hospital for their COPD, a daily score of the maximum 11 points will be assigned [7,48].

Generic health related quality of life (HRQL) of the patients will be assessed by means of the Euro-Qol (EQ-5D-3L). Disease-specific HRQL will be assessed with the Clinical COPD Questionnaire (CCQ) and the Chronic Respiratory Questionnaire – self reported (CRQ-SR). In addition, negative affectivity, social inhibition, and type D personality will be assessed by means of the DS14 questionnaire.

The level of dyspnoea (MRC), effective mucus clearance, physical activity in daily life and motivation will be assessed by standardised questions from the KNGF guidelines [35]. Furthermore, to estimate the patients’ perceived benefit of the physical therapy, the Global Perceived Effect (GPE) will be scored by patients on a 9-point scale [35]. Objective assessment of physical activity in daily life will be done by means of an accelerometer-based activity monitor (Dynaport MoveMonitor) [50].

Height, weight, Body Mass Index (BMI) and Fat Free Mass (FFM) will be measured. The peripheral muscle strength of the patient will be measured as maximal voluntary isometric contraction (MVIC) of the dominant hand, shoulder abduction and knee extension (m. quadriceps), tested in standardised positions by means of the break method by a handheld dynamometer [42,51]. Functional exercise capacity is measured by the six-minute walk test (6MWT), in accordance with the guidelines by the American Thoracic Society [52]. If a straight floor-walking course of 30 metres is not available in the physical therapy practice, a course with a distance of 10 metres is the required minimum [35]. Outcome is measured by total walking distance in metres (6MWD) and in percentage of the predicted value. Reference equations by Hill et al. (2011) will be applied to calculate the predicted value if a straight 30 metre walking course was used, whereas reference equations for a straight 10 metre walking course may be necessary to develop within this study, as no reference equations exist for this frequently used test layout [53]. During the walk test, perceived fatigue and dyspnoea will be measured on a modified Borg scale ranging from zero (nothing at all) to ten (very, very severe) [42]. Transcutaneous oxygen saturation and pulse rate will be measured with a finger pulse oximeter (Onyx 9500) [52]. The modified Get Up and Go test (mGUG) is used to measure basic functional mobility. The outcome is the time it takes a subject to stand up from a chair and walk a distance of 10 metres [54]. After the mGUG, perceived exertion is measured with the modified Borg scale.

Comorbidities of all participants will be recorded thoroughly, as well as smoking history (pack years and cessation moment) and physical therapy compliance (scored by the therapist as insufficient, moderate or good and scored whether comorbidity has any influence on this compliance), as being important potential confounders in this study. Number and type of adverse events will be registered during the one-year treatment period. After randomisation, patients are discouraged to participate in interventions other than those in the study (like hydrotherapy or drug studies) that may influence the outcome measures. When they still decide to participate in other interventions, these interventions will be registered during the study period.

Finally direct and indirect costs will be assessed with three-monthly retrospective questionnaires, including questions about health care contacts, medications use, residential status, occupational status, domestic care service and use of medical aids. The economic evaluation will be analysed from a societal perspective. This means that the most appropriate set of costs captured from the data, regardless of where the costs or benefits occur, will be applied.

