### Physical exercise training to reduce COPD exacerbation frequency, duration or severity

Patients with COPD often experience sudden worsening of symptoms, i.e. exacerbations. Previous studies already demonstrated that physical exercise training (the component that has shown to provide the most benefit of pulmonary rehabilitation programmes) [1] has important benefits for patients, such as improved exercise capacity and HRQL [9,15,24]. However, the effect of pulmonary rehabilitation and physical exercise training on the occurrence of exacerbations is less clear [4,19,25,26]. Observational studies demonstrated that patients who perform regular physical activity have a reduced risk of hospital admission due to COPD and decreased all-cause and respiratory mortality [12,27,28], but neither of these outcomes are a substitute for reduction of exacerbation frequency, duration or severity. The factors determining utilisation of health care resources in patients with COPD are poorly understood [29]. Few studies reported significantly fewer exacerbations after a pulmonary rehabilitation program (including physical exercise training) [30,31]. Reduction of exacerbations may be at least one of the factors explaining the reduction in health care utilisations as reported in observational studies. Moreover, a recent study suggested that an acute bout of exercise resulted in a reduction in sputum proinflammatory cytokines, suggesting some anti-inflammatory effect of exercise in the airways of patients with COPD [32]. Based on these few findings it is plausible to hypothesise that physical exercise training for patients with COPD may result in fewer exacerbations, or at least in less severe exacerbations, meaning exacerbations with a shorter duration or exacerbations without the necessity for hospital admission.

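### Exacerbation duration and severity are defined only for exacerbations that occur, so comparing arms on them is not a randomised comparison; symptom-based duration also has two definitions

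*Protocol article*

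**What the plan says.** Under Secondary outcome measures, the lead definition is: "Exacerbation duration is defined as the duration of the medical intervention per occurrence and the number of days with clear increase of respiratory symptoms". The same paragraph then says, for the symptom-based approach, that "the duration of an exacerbation will be equal to the time between onset and resolution of exacerbation based on the above mentioned definitions". Those definitions stand under 2. Symptom based approach. An episode resolves on the first day of either "three successive days that the patient has returned to his normal health state" or "seven consecutive days on which patients continuously reported no or only a ‘slight increase’ in symptoms, compared to baseline", the second rule also requiring no fever and no change in sputum colour.

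Severity has two forms. For the event-based approach, "a scale for exacerbation severity is proposed, which distinguishes two levels of exacerbation severity", and each exacerbation receives one of them. For the symptom-based approach, "the severity of an exacerbation day will be calculated with help of symptom scores".

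The Background hypothesis is that training "may result in fewer exacerbations, or at least in less severe exacerbations, meaning exacerbations with a shorter duration". Study aim lists frequency, duration and severity together. Primary outcome measure treats successive exacerbations as independent. Data analysis (Clinical effectiveness) assigns linear regression and generalised linear models to the secondary outcomes and does not name the unit of analysis for duration or severity. Size of the study population expects a 22% difference in exacerbation rate.

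**The concern.** Duration and severity, as defined, exist only for patients who have an exacerbation after randomisation. The treatment is meant to change who has one and how many. If it succeeds, the exacerbations left in the two arms come from differently selected patients and events, and randomisation no longer protects the comparison. A difference in mean duration or in the share of severe events could then come from which events were prevented rather than from any change in the events themselves.

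Two further problems follow from the text. A patient with several exacerbations contributes several related durations; analysed as independent observations, these overstate precision. And two definitions of symptom-based duration leave open which number is to be computed from the same diary.

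Duration and severity are two of the three exacerbation aims, so these are not incidental endpoints.

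**Working it through.** **Figures in the plan.** The plan gives no expected duration or severity. The one figure in the severity definition is consistent: three major symptoms at up to 2, four minor symptoms at up to 1, and fever at 1 give 3 × 2 + 4 × 1 + 1 = 11, the stated maximum. The 79 patients per group cannot be reproduced uniquely because no control rate is given; nothing below depends on it.

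**1. One-patient illustration (assumed durations).**
- Control course: 5, 5, 15 and 15 days. Mean (5 + 5 + 15 + 15)/4 = 10; total 40.
- One short exacerbation prevented: 5, 15 and 15 days. Mean 35/3 = 11.7 (+17%); total 35 (−12.5%).

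The mean per occurrence worsens although the patient has fewer exacerbation days.

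**2. At the expected effect size.** Read the 22% as a relative reduction in rate (the plan does not say whether it is relative or absolute) and assume that every prevented event is short. Let s be the share of short events in the control arm, and a and b the short and long durations.
- Control mean = s·a + (1 − s)·b.
- Short share in the treated arm: s′ = (s − 0.22)/0.78.
- Treated mean = s′·a + (1 − s′)·b.
- Ratio of total days = 0.78 × treated mean / control mean.

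With s = 0.7, a = 7 and b = 14:
- Control mean = 4.9 + 4.2 = 9.1 days.
- s′ = 0.48/0.78 = 0.615, so treated mean = 9.7 days.
- Ratio of total days = 0.78 × 9.69/9.1 = 0.83, a 17% fall.
- If long events are also the severe ones, the severe share rises from 30% to 38.5% while severe events per patient do not change.

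With s from 0.5 to 0.8, and (a, b) of (7, 14), (7, 21) or (5, 15), the mean per occurrence rises by 5% to 14% while total days fall by 11% to 18%.

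If prevention is unselective, s′ = s. The mean per occurrence does not move and total days fall by 22%.

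**3. Who enters the comparison.** Assume patient rates vary as a gamma distribution with shape 1. The share of patients with any event is then λ/(1 + λ), where λ is the mean number of events.
- Control λ = 1: 1/2 = 50% in control against 0.78/1.78 = 44% treated.
- Control λ = 2: 2/3 = 67% against 1.56/2.56 = 61%.

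A third to a half of control patients, and more of the treated, would contribute nothing to a per-occurrence comparison.

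**4. The two symptom-based definitions.** A clear day here is one that meets the onset criterion.

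| Diary, then normal days | Days with clear increase | Onset to resolution |
|---|---|---|
| 5 clear, 4 slight | 5 | 5 |
| 3 clear, 4 slight, 2 clear | 5 | 9 |
| 4 clear, 5 slight with changed sputum colour | 4 | 9 |

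In the first row, seven consecutive days of slight or no increase begin on day 6, so both rules stop at 5. In the second, the run of slight days is broken before seven, so resolution falls on day 10. In the third, changed sputum colour blocks the seven-day rule; this row assumes that changed colour alone does not make a day clear.

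**The case against.** The strongest reply is that the definitions only say how one exacerbation is measured. Any event must be measured singly before it is summed per patient, and Data analysis neither restricts the secondary analyses to patients with events nor names a unit. Its sentence on using all exacerbations of each patient may concern the primary count alone. Unit, zeros and clustering could be settled in a fuller plan.

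This stands in large part for severity: the two-level scale supports a count of severe events per randomised patient equally well, and a daily score can be summed. The per-exacerbation comparison of severity is therefore inferred. It stands less well for duration. The article fixes medical-intervention duration per occurrence, frames the hypothesis as shorter exacerbations, and states an independence assumption. Followed as written, that leads to the conditional comparison.

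Three stronger readings are tempting and are not supported.
- **The trial would report harm where there is benefit.** Reversal needs prevention to fall mainly on short or mild events, and nothing in the documents establishes that. Exacerbation frequency is the primary outcome and would show the reduction alongside.
- **Onset to resolution always adds the slow recovery days.** The seven-day rule dates resolution to the first of those days. Four clear days followed by ten uninterrupted slight days, without fever or changed sputum, give 4 days under both definitions.
- **Event-based duration is invalid because it follows the length of treatment.** The Discussion already concedes that health care use is an imperfect substitute and adds the symptom-based approach for that reason.

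**Conclusion.** The point holds for the secondary outcomes. As defined, duration has no value for a randomised patient without an exacerbation. A between-arm comparison on that basis is not protected by randomisation and, under the stated independence assumption with ordinary regression, ignores correlation within patients. For severity the same conclusion rests on inference.

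The size is illustrative. With a 22% relative reduction confined to short events, mean duration per occurrence would rise by 5% to 14% while total days fall by 11% to 18%. The event mixes and durations are assumptions, and unselective prevention leaves the mean unchanged. The loss of a randomised comparison does not depend on these figures; the direction and amount of bias do.

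The two symptom-based definitions differ in the text itself. They agree in simple recoveries and part when symptoms fluctuate or sputum colour stays changed. The primary exacerbation count is not affected.

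**What to change.** In Secondary outcome measures and Data analysis:

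- Make the between-arm secondary outcomes total exacerbation days per patient-year and number of severe (hospital or emergency) exacerbations per patient-year. Include all randomised patients, with zero for those without events.
- Analyse both with a count model with an offset for time observed. Days come in runs, so the variance for total days must allow for overdispersion.
- Keep one symptom-based duration, from onset to resolution under the rules in 2. Symptom based approach, and remove the count of clear-increase days from the lead definition.
- Report duration and severity per exacerbation descriptively, with standard errors clustered by patient.

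The cost is wording only; the daily diaries and records of health care contacts already supply the data. The drawback is that total days mixes frequency with duration, which is why the per-exacerbation figures should stay as description.
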